### **III. Subject Participation**

#### **A. Recruitment:**

1. Participants will be recruited from the KU Center for MS Care.
2. [name], as the Medical Director of the KU Center for MS Care will recruit through her clinics and patients. Other members of the study team, particularly the PI and research technician, will also be involved in recruitment.

**B. Screening Interview/questionnaire:** The screening visit will be conducted at the KU Center for MS Care by [name], the PI and a GRA. [name] will pre-screen potential participants for medical history and EDSS inclusion/exclusion criteria before subjects are approached for recruitment. The PI and [name] will administer the Mini-Cog questionnaire and the Fried phenotype to complete the screening.

#### **C. Informed consent process and timing of obtaining of consent**

- 1 The PI ([name]) will give participants a detailed and comprehensive information about the study and will obtain their written consent, with assistance from [name].
- 2 The consenting process will take place in a private room in the Landon Center on Aging, to give the participant privacy. The participant will be sent the informed consent form via email prior to the assessment visit so they have time to review the document prior to consenting, if they wish. The participant will be encouraged to ask as many questions as needed and will be reminded that they have as much time as needed to make a decision. The participant will be given a copy of the signed informed consent. Original copies will be stored securely in a locked cabinet and virtual copies of the document will be stored in a secure location such as a P: drive or REDCap.
- 3 We expect all of our participants to be able make the informed consent decision themselves. [name] will use her clinical expertise to determine if patients she recruits are able to make their own decisions. Additionally, subjects with severe cognitive impairment (as determined by a Mini-Cog score <3) will be excluded from the study to ensure that participants are able to consent for themselves. If the PI, during the informed consent process, feels that the subject is unable to consent for themselves, they will be excluded from the study.

**D. Alternatives to Participation:** Subjects will be reminded that participation in this research project is completely voluntary and they can decide to not participate and/or to withdraw consent at any point without giving a reason, and without their care being affected.

**E. Costs to Subjects:** There will be no costs to participants in this research project.

**F. How new information will be conveyed to the study subject and how it will be documented:** Subjects will be informed of new information through a call from the study team. The study team will document the call and the participant's response.

**G. Payment, including a prorated plan for payment:** Participants will receive up to \$190 dollars if they participate in the entire study. Participants will receive \$50 for each of the following visits: the baseline assessment (Visit 2) and the post-training assessment (Visit 3). The participants will receive \$5 for each of the 18 training visits. Participants will only be paid for the visits they have completed. If a participant drops out or withdraws, they will only be paid for the visits they have already attended. Participants will be paid via Clincard.

**H. Payment for a research-related injury:** Participants will not be able to pursue financial compensation should they be injured as a result of participating in this research. However, they are not precluded from seeking to collect compensation for injury related to malpractice, fault, or blame on the part of those involved in the research, including the institution.

#### **IV. Data Collection and Protection**

##### **A. Data Management and Security:**

1. The study team will have access to the study data. Access to data will vary according to study team member role. The PI will have the highest-level access to data.

2. Subject confidentiality will be maintained by assigning participants a study ID so that records will not be directly linkable to them (see below). Records will be retained per university policies.
3. Human subjects will be identifiable through coded information. Subjects will be assigned a screening and study ID.
4. Only the PI and Co-I [name] will have access to the key to the code, or the "master key."
5. Participants will be given a unique study ID to protect their confidentiality. Except for the master key, no other data will have a direct link between the participant's name and the study ID. Therefore, participant names will not be on data, but rather, their study ID. Participants will have a screening ID, and once they pass the screening, a study ID.
6. High-risk data will be stored on either a P: drive provided by the university or on REDCap. Medium risk data will be stored on a university S: drive and on REDCap. Paper copies of study forms will be stored in locked cabinets.
7. Mobile devices will not be used for data collection or storage.
8. Identifiable data will not be sent outside KUMC.

**B. Sample / Specimen Collection:** Blood samples will be collected by trained nurses at the Landon Center on Aging (LCOA) following standard procedures. The blood samples will be destroyed immediately after the analysis has been conducted. LCOA staff will share the results of the blood analysis only with the research team and will use the study ID rather than the participants' personal information.

**C. Tissue Banking Considerations:** N/A.

**D. Procedures to protect subject confidentiality:** Participant confidentiality will be maintained by performing informed consent and procedures within a private space at the LCOA. Participants will be assigned a unique study identification number, and all study forms will be de-identified. These forms will only contain the unique study identification number, thereby ensuring participant confidentiality. After the completion of the study, other researchers will have access to the de-identified study data. This will enable others to address additional questions and further investigate the results of the interventions.

**E. Quality Assurance / Monitoring**

1. Trained research personnel will perform monitoring weekly to assess for data entry errors, outliers, and missing data. Personnel will also perform audits quarterly to assess adherence to the protocol, informed consent documents, source documents, regulatory documents, signature lists, screening lists and enrollment logs. The option to mark data forms for missing or incorrect data will be utilized in REDCap.
2. Third party monitoring. N/A.

**V. Data Analysis and Reporting**

**A. Statistical and Data Analysis:** Descriptive statistics (frequency/percent and mean/SD) will be mainly used to summarize participants' characteristics and intervention outcomes. The means and 95% CIs for pre-post changes in the primary (i.e., frailty index) outcome will be estimated. No imputation will be considered for missing data. The Wilcoxon rank sum test will be used for comparing the pre-post changes in frailty index between the two groups.

- B. Outcome:** The intervention will be considered feasible if the retention rate and the proportion of completed sessions are more than 80%. We expect that at least 80% of participants will complete the multimodal exercise training and that no serious adverse events will be recorded during the training sessions. We expect that participants in the experimental group will have greater reduction in frailty index than participants in the control group. Finally, we expect that participants randomized to multimodal exercise will also exhibit a clinically meaningful change in the frailty index.
- C. Study results to participants:** A short, written letter of the study results will be sent to participants once the study has concluded.
- D. Publication Plan:** Findings from this study will be presented at scientific conferences and published in research journals.

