**Aim 1: To determine the feasibility of a multimodal exercise training in pwMS.**

We hypothesize that at least 80% of participants will complete the multimodal exercise training and that no serious adverse events will be recorded during the training sessions. In addition to feasibility, we will also generate the effect sizes from the intervention, which will inform the development of a fully powered randomized controlled trial (RCT).

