## **II. Research Plan and Design**

**A. Study Objectives:** The broad research goal of this study is to provide novel data regarding the potential efficacy of multimodal exercise to reduce frailty in pwMS and will set the foundation for our long-term goal of identifying novel interventions to improve the quality of life of persons with MS. The specific aims of the project will be to determine the feasibility of a multimodal exercise training in pwMS (Aim 1), and to explore the effects of the multimodal exercise training on frailty in pwMS (Aim 2).

**B. Study Type and Design:** Using a pilot single-blind randomized controlled trial (RCT) study design, ambulatory individuals living with MS will be allocated to 6 weeks of multimodal exercise training (n=30) or to a waitlist control group (n=30) (Figure 1).

[figure not shown]

Figure 1. Study design.

The following outcomes will be collected to accomplish the study aims:

**Aim 1: Feasibility Outcomes:** The following outcomes, based on the guiding principles for feasibility studies, will be utilized to examine the feasibility of the Virtual Reality and Resistance Training for MS (VRRT4MS) program in the study population: a) participant recruitment, i.e., number of consented individuals/number of approached individuals (expressed as a percentage); b) retention rate, i.e., number of participants completing the intervention/number of participants enrolled at baseline (expressed as percentage); c) appropriateness of data collection and training procedures, as quantified through the percentage of missing data for analysis purposes (i.e., missing items in the frailty index) and through time spent in training, respectively; d) participant safety, i.e., number of adverse and serious adverse outcomes throughout the study and self-reported pain, assessed by the numeric pain rating scale, during each training session (the Borg and Omni scales of perceived exertion will also be administered throughout each training session to differentiate exertion from pain); e) evaluation of resources, i.e., difference between proposed and actual research timeline; f) user engagement, i.e., study participant feedback questionnaire. We note that the effects of VRRT4MS on the primary frailty outcome, namely the frailty index (AIM 2), will also represent a further feasibility outcome of the intervention.

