of the committee. The members of the DSMB will also receive regular data reports at a schedule agreed upon by the members. Types of analyses to be performed: Analysis of completion, accuracy, and correct and timely response to events, data quality, protocol-adherence and attrition. Safety-related triggers that would cause the PI to stop or alter the study: unanticipated serious adverse outcome to participant. The major tasks of the DSMB will be to (1) assess whether there are safety findings that require stopping or modifying the study and (2) adjudicate Serious Adverse Events and deaths that are unexpected and/or atypical for healthy young-old adults. The DSMB will receive un-blinded safety data quarterly. If the DSMB detects safety concerns, then the DSMB may request safety data more frequently. If, at any time during the study, the perceived risk/benefit of treatment changes, the DSMB has the authority to recommend protocol modification or study curtailment. During the course of the trial, the DSMB will receive information from concomitant trials performed or published elsewhere. In addition, the DSMB will receive periodic reports about recruitment and safety information. Based on information received during the trial, the DSMB may choose to recommend changes to the protocol. If protocol changes are necessary, the implementation of changes will avoid unmasking the accumulated outcomes to the clinical trial personnel who are responsible for the ongoing performance of the trial. If there are unforeseen safety hazards that emerge during the clinical trial, then the Data and Safety Monitoring Board will have the authority to recommend temporary or permanent cessation of the trial.

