When research personnel learn that a participant has experienced an adverse event, research personnel will contact the PI on the same day to receive instructions for the transfer of the participant for treatment and follow-up of the adverse event. In addition, research personnel will complete an adverse event form. Participants with adverse events are eligible to remain in the trial unless there is withdrawal of consent. Participants who have experienced a serious adverse event will be withdrawn from the study.

The investigator will communicate with the participant and primary care physician (if deemed necessary by PI) to acquire information to complete the treatment questions on the adverse event form. The specific questions are: no action taken (i.e., further observation only); intervention temporarily interrupted; intervention permanently discontinued due to this adverse event; patient hospitalized. The investigator will continue to communicate with the participant and primary care physician until resolution to record change of severity, change of suspected attribution to intervention, and change of treatments for the adverse event.

The investigators and the Data and Safety Monitoring Board will review Adverse Events and Serious Adverse Events. If unexpected experimental-related adverse events emerge during the course of the trial, then the investigator will report the adverse events to the Institutional Review Board and the National Institutes of Health within the timelines required by each entity.

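### The feasibility rule has no serious-adverse-event condition and a different 80% cut from Aim 1, so its verdict can disagree with the Aim 1 hypothesis

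*Protocol*

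**What the plan says.** Aim 1 (Protocol, I.A) has two parts: "at least 80% of participants will complete the multimodal exercise training and that no serious adverse events will be recorded during the training sessions".

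The rule that turns data into a verdict appears in the same words in II.C and V.B: "The intervention will be considered feasible if the retention rate and the proportion of completed sessions are more than 80" per cent. It has no safety term, its inequality is strict, and it adds a session condition that Aim 1 does not mention. In V.B the next sentence restates Aim 1, but only as an expectation: "We expect that at least 80% of participants will complete the multimodal exercise training and that no serious adverse events will be recorded during" (meaning sessions of training).

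Four other statements bear on the point:

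- II.B lists safety among the feasibility outcomes, without a threshold: "participant safety, i.e., number of adverse and serious adverse outcomes throughout the study and self-reported pain".
- II.B defines retention: "retention rate, i.e., number of participants completing the intervention/number of participants enrolled at baseline (expressed as percentage").
- II.L says how affected participants are handled: "Participants who have experienced a serious adverse event will be withdrawn from the study".
- II.L also gives a trigger: "Safety-related triggers that would cause the PI to stop or alter the study: unanticipated serious adverse outcome to participant".

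**The concern.** The verdict on feasibility is the only formal decision rule in the protocol, and it is meant to support a larger randomised trial. A rule of this kind should return a positive answer only when the hypothesis behind it is supported. Here the hypothesis joins completion with absence of serious events in training, and the rule looks only at retention and attendance. II.F names falls with head injury or fracture as possible harms of training, so the omitted condition matters.

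The protocol fixes this rule itself, twice, so the point is not detail that could be left to a statistical analysis plan. There is also a smaller mismatch in the cut (at least 80% against more than 80%), and V.B carries both in consecutive sentences.

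**Working it through.** **Inputs.** Exercise arm n = 30 (II.B). 18 sessions each (II.E), so 30 × 18 = 540 scheduled. Dropout 15% and at least 24 completers per group (II.C). Participants with a serious event are withdrawn (II.L). I take the exercise arm as the denominator for retention and all 540 scheduled sessions as the denominator for attendance; the protocol states neither.

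**The plan's own figure.** 30 × (1 − 0.15) = 25.5, so at least 24 is consistent as a floor. 24/30 = 80.0% corresponds to 20% dropout.

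**What each statement requires.**

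| | Aim 1 hypothesis | Rule (II.C, V.B) |
|---|---|---|
| Completers of 30 | ≥ 24 (80.0%) | ≥ 25 (83.3%) |
| Sessions of 540 | not mentioned | ≥ 433 (80.2%) |
| Serious events in sessions | 0 | any number |

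**Direction 1: feasible although the hypothesis is false.** Each participant with a serious event is withdrawn and costs one completer.

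- One event, no other loss: 29/30 = 96.7% retained. If the others attend fully, sessions are at least 29 × 18 = 522, and 522/540 = 96.7%. The rule passes and the hypothesis is false.
- One event plus four ordinary dropouts, close to the 30 × 0.15 = 4.5 losses planned: 25/30 = 83.3%, which still passes on retention. If the five leavers contributed no sessions, the 25 completers would need 433/25 = 17.3 of 18 sessions on average. Any sessions that leavers attended would lower that.
- Extreme, with no dropout for any other reason: five events leave 25/30 = 83.3% and, with full attendance by the rest, at least 25 × 18 = 450 sessions, 450/540 = 83.3%. The rule passes with an event proportion of 5/30 = 16.7% (exact 95% CI 5.6% to 34.7%). A sixth event gives 24/30, which fails.

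**How likely, under assumptions.** The protocol gives no serious-event rate for this programme. Let s be the assumed risk per participant of a serious event in training, and c the completion among those without one. On the retention condition alone, and if the trial continues unchanged:

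P(retention cut met with ≥ 1 event) = P[Bin(30, (1 − s)c) ≥ 25] − (1 − s)^30 × P[Bin(30, c) ≥ 25].

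For s = 2% and c = 90%: 0.865 − 0.545 × 0.927 = 0.36.

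| s (assumed) | c = 85% | c = 90% | c = 95% |
|---|---|---|---|
| 1% | 0.14 | 0.21 | 0.26 |
| 2% | 0.23 | 0.36 | 0.44 |
| 5% | 0.32 | 0.54 | 0.72 |

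**Direction 2: not feasible although the completion hypothesis is true.** Comparing the cuts for each completer count out of 30, they differ only at 24. There ≥ 80% holds and > 80% does not. The probability of exactly 24 is 0.18, 0.14 and 0.05 for true completion of 80%, 85% and 90%. No completer count passes the rule's cut while failing the hypothesis's cut.

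**The case against.** The strongest defence is that safety is deliberately kept apart. II.B lists six kinds of feasibility outcome and only retention and training delivery have cut-offs. Serious events are counted, a safety board reviews unblinded safety data quarterly, and an unanticipated serious outcome can stop or change the trial. V.B puts the zero-event expectation directly after the rule. II.F reports no serious events among 108 people in the virtual reality intervention on which this programme builds. A pilot may reasonably use an adherence threshold that is not identical to its hypothesis.

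Part of this stands. Judging safety separately is legitimate, and a reader who inferred that the protocol ignores safety would be wrong. But the protocol does not say that its verdict excludes safety. Aim 1 makes safety half of the feasibility hypothesis, and neither the board's review nor the trigger is tied to the word feasible. The earlier record does not make an event negligible: with 0/108, taking all 108 as exposed, the exact two-sided 95% upper limit is 1 − 0.025^(1/108) = 3.4%. That intervention also lacked the resistance component. The limit covers the 1% and 2% assumptions above but not the 5%.

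Three stronger readings are tempting and not supported:

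- **The changed cut also helps produce a false positive verdict.** It cannot, because the strict inequality is the harder one to meet.
- **The protocol expects 24 completers and so plans to fail its own rule.** 24 is its floor; the expectation is 25.5, and 25 or 26 completers pass on retention.
- **Five serious events is a typical scenario.** It needs no other dropout, against the 15% planned, and a trial that ran on unchanged despite the trigger.

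**Conclusion.** The rule and the hypothesis do not match, and following the rule as written can contradict Aim 1 in two separate ways. The omitted safety condition allows a verdict of feasible with one or more serious events in training, up to five of 30 at the extreme. The strict cut gives a verdict of not feasible at exactly 24/30, where the completion hypothesis is met. The first is the more important; the second matters at one value only.

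The counts rest on the exercise arm as denominator, on withdrawal after a serious event as II.L states, and on 540 scheduled sessions. The table of probabilities also rests on assumed event risks and completion rates that the protocol does not give. It shows only that the conflict need not be remote.

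**What to change.** Use one inequality, at least 80% as in Aim 1, in I.A (Aim 1), II.C and V.B, and carry Aim 1's safety condition into the rule. Suggested wording for II.C and V.B: *The intervention will be judged feasible only if retention and the proportion of completed sessions are each at least 80% and there is no serious adverse event in any training session.*

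If the sponsor prefers to judge safety separately, or to count only events related to training, that is open to it, but Aim 1 must then say the same. A relatedness condition added to the rule alone would leave it at odds with Aim 1, which has none. Where safety is judged separately, the verdict should be labelled as covering adherence and retention only.

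In every case, report the serious-event proportion with an exact two-sided 95% confidence interval. With no events in 30 the upper limit is 1 − 0.025^(1/30) = 11.6%, which shows how little a clean result would exclude.

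**Cost.** A sentence or two in each of three places, settled before results are known, with no change to sample size. Relaxing the cut raises the chance of meeting the completion condition from 0.711 to 0.847 at a true completion rate of 85%, and from 0.428 to 0.607 at 80%. The downside of the safety condition is that a single serious event in a session blocks the verdict. At an assumed risk of 1% or 2% per participant, at least one event among 30 has probability 1 − 0.99^30 = 0.26 or 1 − 0.98^30 = 0.45. The sponsor should accept that knowingly or take the separate-judgement route.

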## **APPENDIX I: VULNERABLE POPULATIONS**

- I. Vulnerable populations are not being recruited.
- II.
